## Abstract

**Objective:**

Acupuncture therapy for chronic low back pain (CLBP) has received increasing attention. Nevertheless, the evidence of efficacy and safety of random controlled trials (RCTs) remains controversial. Acupuncture as a complex intervention influenced by many factors, its effectiveness in treating chronic low back pain in the real world is unknown. We will develop a network-based registry study to evaluate the effectiveness and safety of acupuncture for the treatment of chronic low back pain and explore key factors affecting efficacy in the real world.

**Methods:**

A prospective, multi-center and dynamic registry study. All acupuncture related information will be collected through a high-quality structured network platform. Patients with CLBP included in the study met the following criteria: age from 16 to 80 years, using acupuncture as a main therapy and voluntarily signing the informed consent. At least 2000 patients, 27 acupuncturist, and 9 medical centers will be recruited under actual clinical settings at the first stage. Numeric rating scale (NRS), Oswestry Disability Index (ODI) and Effective rate will be measured in pain and functional disability assessment, respectively, as the primary outcome. Evaluation index will be collected at the baseline and follow-up in 1, 4, 12 weeks after the last visit. Hierarchical models and regression analysis will be used to explore the key factors affecting acupuncture effectiveness. Effects between propensity matching groups (Traditional Chinese acupuncture style vs Microacupuncture style, Local acupoint selection vs Non-local acupoint selection, Single Acupuncture vs Combined therapy) will be compared.

**Discussion:**

This study will be conducted based on the characteristics of acupuncture therapy in the “Real World”. Fundamental factors affecting the clinical effectiveness of acupuncture and the preferred acupuncture regimen in the treatment of CLBP will be identified. Reliable acupuncture evidence for the treatment of CLBP through the registry will be a significant supplement to the RCTs.

**Trial registration:**

Chinese Clinical Trial Registry, ChiCTR-OOC-17010751 and Acupuncture-Moxibustion Clinical Trial Registry, AMCTR-OOO-17000045. Registered date on 3 December 2016.

## Background

As a consequence of the acceleration of global aging, sedentary lifestyle increasing and average weight gain, chronic low back pain (CLBP) has become a global condition with high incidence. Although disability and financial burden attributed to chronic low back pain is substantially different between countries, the incremental impact of the worldwide health care system predicted to tremendously in the coming decades [1]. According to 2015 global statistics, low back pain accounts for 7.3% point prevalence of activity-limiting illnesses, affected 5.4 billion people at all ages [2]. CLBP accounts for a significant portion of the $100 billion spent annually on treatment in the United States [3]. In China, back pain kept the top one disorder that causes of years lived with disability(YLDs) from 1990 to 2010 [4]. Therefore, effective and safe treatment is especially crucial in overcoming low back pain and disability related to the chronic condition.

In a variety of treatment options devoted to back-related disability and chronic pain consequence, non-invasive treatment therapies captured more attention. Changes can be verified in recent guidelines for low back pain [5–7]. Interventional procedure and operation are limited to recommend in guidelines, as well as the pharmacotherapy, in consideration of efficacity, safety and accessibility. Moreover, nonpharmacological intervention was recommended as first-line treatment, which included acupuncture, massage, spinal manipulation, and yoga [6]. As a characteristic non-pharmaceutical option against the opioid crisis, acupuncture captured particularly concerning in pain relief. On account of safety and the actual effect, acupuncture is widely accepted in the management of chronic low back pain [8, 9]. Low back pain was the top 1 frequently treated indication in US’s acupuncture clinic according to a cross-sectional study [10]. However, there is a lack of basic dataset on the use of acupuncture to treat CLBP in China and abroad, including the effective population characteristics, reasonable acupuncture session, preferred acupuncture protocol and acupuncture implementation details, etc.

Durable efficacy of acupuncture was reported to improve function and alleviate pain for CLBP patients at the individual level [11]. Nonetheless, contradictory results are subsistent [12, 13], that acupuncture efficacy was no better than comforting acupuncture or sham acupuncture [14–16]. Despite negative outcomes of acupuncture for CLBP is not uncommon to discover [13, 14, 17], controversy, and doubting exist in methodological, research environment, unreasonable comparison, multiple acupuncture interventions and study population [18–20]. Firstly, as a complex intervention featured with specific and nonspecific factors [21], acupuncture is not suiting RCT research paradigm that was initiated more appropriately for drug and biomedically-oriented interventions [20]. RCTs is usually limited to strictly selected patients, highly controlled conditions and using a sham intervention so that results are poorly generalizable to real clinical practice [22, 23]. Secondly, very little evidence for CLBP in the special populations such as elder or some subtype of CLBP [24]. Obviously, under real clinical settings, older adults have a higher incidence of CLBP and are likely to suffer more complications [24, 25]. Furthermore, not only the acupuncture style or type, implementation details, treatment duration and frequency of acupuncture can affect outcomes, but also the experience of the operator, the individual conditions that lead to CLBP and the combined treatment too [26, 27]. The lacking of acupuncture experience and perception in the social context may reduce the effectiveness of acupuncture. Most of RCTs was conducted under non-eastern culture, recruited patients lacking acupuncture experience, De Qi perception or cognition were inevitable [28]. Doubtlessly, new research models need to provide more practical details to bridge the gap between rigorous controlled circumstances and real-world practice.

Therefore, we intend to conduct a registry of acupuncture therapy for CLBP through a network platform rooted in the reality of diverse form and operations of acupuncture. This is a prospective, multi-center, registry study. The current status of the study is in recruiting.

The objectives of the study:
To develop an international registration platform of CLBP for acupuncture therapy;To identify the key factors affecting the clinical effectiveness of acupuncture in treating CLBP from the perspective of acupuncture implementation and physicians;To analyze population characteristics and subtypes of CLBP suitable for acupuncture.

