### Inclusion criteria

Chronic low back pain or acute onset of chronic low back pain were observed as the main objects to meet the diagnostic criteria for chronic low back pain.16 years≤Age ≤ 80 years;The main treatment method is acupuncture.Voluntarily participate in the patient registration study and sign informed consent.

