#### Effective rate

Minimal clinically important difference (MCID) is an index to identify effective group, that is the NRS score decreased by 2 points or ODI score cut down 10 points [36]. The effective number divides the total number of people included in the analysis is the effective rate.

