#### Analytic approach

Data with poor compliance, non-compliance with the study program or missing important information are not included in the analysis. Data processing and statistical analysis will use SPSS version 24 (IBM Corp., Armonk, NY, USA) and SAS Version 9.4 (SAS Institute Inc., NC 27513–2414, USA).

We will select 1-week,4-week,12-week, assessments respectively at evaluation time point on the ODI and NRS index. Firstly, baseline characteristics comparability needs to be assessed between the propensity-matched groups. Model adjustment suggested by Rosenbaum and Rubin will be adopted to conquer residual covariance imbalances [42]. Secondly, multivariate linear regression models will be employed to adjust the propensity score and baseline characteristics. Once matched, change in ODI and NRS between-group at different observation points will be calculated by paired t-test. Thirdly, logistic regression models will be used to evaluate the magnitude of impacts contributed by baseline factors on acupuncture effectiveness for CLBP patients. Descriptive analysis will be used for variables such as the recruited research center,s basic characteristics of doctors and patients, initial diagnosis and intervention details. Quantitative data (Height, Weight, NRS, ODI, etc.) will be described by mean, standard deviation, median, maximum and minimum values. The enumeration data (Acupuncture style, Acupoint selection principle, Operation of acupoints, Effective rate etc.) and ranked data (Educational background, Physician title) will be described by numbers, percentages, rate and constituent ratio. If necessary, parametric methods or alternate nonparametric methods will be selected appropriately.

We will adopt the propensity score matching of patients at 1:1 to imitate an RCT. Baseline confounder will be equilibrated and matched on variables such as demographic data, medical history, duration, intensity, back function. The comparative analysis will be conducted after the baseline unevenness adjustment. Propensity score will match comparison group, such as Traditional Chinese acupuncture style vs Microacupuncture style (Scalp acupuncture, Ear acupuncture, Wrist and ankle acupuncture, Eye acupuncture, Umbilical acupuncture, Abdomen acupuncture), Local acupoint selection vs Non-local acupoint selection and Single Acupuncture vs Combined therapy etc.

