Hierarchical models based on the pain grading, medical center, age group, gender, TCM syndromes and classification of diseases will be taken into account to explore the important factors affecting the effectiveness of acupuncture for CLBP [43–45]. Conditional logistic regression models adjusting by different variables to identify predictors of long-term effectiveness presented by ODI and NRS or recurrence at the12-week follow-up.

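### With every patient on acupuncture, the planned models find factors associated with improvement among treated patients; they cannot show who is suited to acupuncture or how effective it is

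*Protocol article*

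**What the plan says.** The aim in the abstract is stated as "We will develop a network-based registry study to evaluate the effectiveness and safety of acupuncture for the treatment of chronic low back pain". The third objective, at the end of the Background, is "To analyze population characteristics and subtypes of CLBP suitable for acupuncture". The Discussion adds that the characteristics of cases in which acupuncture does not work will be identified.

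The Inclusion criteria require that "The main treatment method is acupuncture", so no patient without acupuncture is registered. They also admit flares: "Chronic low back pain or acute onset of chronic low back pain were observed as the main objects". Neither the diagnostic nor the eligibility criteria set a minimum NRS or ODI score.

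The section Effective rate defines success by change within the patient: "that is the NRS score decreased by 2 points or ODI score cut down 10 points".

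Under Analytic approach, "logistic regression models will be used to evaluate the magnitude of impacts contributed by baseline factors on acupuncture effectiveness for CLBP patients". A further set of models covers subtypes: "Hierarchical models based on the pain grading, medical center, age group, gender, TCM syndromes and classification of diseases will be taken into account". The propensity-matched comparisons named there set one form of acupuncture care against another: style, choice of points, and acupuncture alone against acupuncture combined with other therapy.

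Limitations of study concedes that there is no pre-defined comparison group and that selection bias and hidden confounding will remain.

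**The concern.** Being suited to a treatment is a statement about a difference: these patients gain more from acupuncture than others do, relative to what would have happened without it. Estimating that needs an interaction between the patient factor and treatment, and so some patients without the treatment. The registry has none. In its data, a fall from baseline combines any effect of acupuncture with natural course, co-treatment and regression to the mean. A factor that predicts the fall may predict it equally under any care.

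Baseline severity is a special case. Success is a fixed absolute fall, and pain grading is one of the named model factors. Patients recorded at a high score tend to score lower next time whatever is done, so severity will appear as a predictor mechanically.

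At stake is what the registry may conclude. Following the plan as written would report prognostic factors as subtypes suited to acupuncture, the effective rate as acupuncture's effectiveness, and poor prognosis as failure of acupuncture.

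**Working it through.** **1. Objective against design.** The third objective and the effectiveness aim each need a contrast with care that does not include acupuncture. The Inclusion criteria admit none, and every matched comparison named has acupuncture on both sides. The logistic and hierarchical models are main-effect analyses of change among treated patients. More analytic detail elsewhere cannot supply the contrast.

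**2. How large could the artefact be?** The article gives no standard deviation, correlation or expected effective rate, so there is no stated figure to reproduce. What follows is an illustration under assumptions.

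From the article: success on NRS is a fall of at least 2 points on a 0–10 scale, and there is no entry threshold.

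Assumed: each patient has a long-run NRS level with mean 5 and between-patient SD *s_b*. Baseline and follow-up each add independent fluctuation with SD *s_w*. Scores are rounded and bounded to 0–10. Treatment effect and time trend are both zero.

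Before rounding, the correlation is ρ = s_b² / (s_b² + s_w²), and the expected fall for a patient at baseline *b* is (1 − ρ)(b − 5). With ρ = 0.50 that is 0 points at b = 5 and 0.50 × 3 = 1.5 points at b = 8, with no treatment effect at all.

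Simulated results (4 million patients per row):

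| s_b / s_w | ρ before rounding | ρ after rounding | Mean fall | Effective, all | Effective at NRS 5 | Effective at NRS 8 | Odds ratio, 8 vs 5 |
|---|---|---|---|---|---|---|---|
| 1.5 / 1.5 | 2.25/4.50 = 0.50 | 0.49 | 0.0 | 24% | 20.7% | 50.7% | 3.9 |
| 1.8 / 1.0 | 3.24/4.24 = 0.76 | 0.75 | 0.0 | 15% | 13.3% | 28.9% | 2.7 |
| 2.0 / 0.8 | 4.00/4.64 = 0.86 | 0.85 | 0.0 | 10% | 9.0% | 17.6% | 2.2 |

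Odds ratio, first row: (0.507/0.493) / (0.207/0.793) ≈ 3.9. Last row: (0.176/0.824) / (0.090/0.910) ≈ 2.2.

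A second set of assumptions (mean 4, SD 2, ρ 0.5 to 0.8, no threshold) gives 23% to 12% effective. In that set, 15% to 9% are effective at baseline NRS 5 or below, against 56% to 27% at 7 or above.

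These rates use NRS alone. If either criterion suffices, adding ODI can only add successes.

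**3. Does a large sample protect?** No. Suppose acupuncture works in nobody, and a factor carried by half the patients moves the effective rate from 30% to 40%. With N = 2000 (1000 per group), the standard error is √[(0.30×0.70 + 0.40×0.60)/1000] = 0.0212. Then 0.10/0.0212 = 4.71 and 4.71 − 1.96 = 2.75, so the factor is declared significant with probability 0.997. With 20% missing (N = 1600) it is 0.988. For 35% against 40% the figures are 0.64 and 0.54. With an added non-acupuncture group of equal size, a test of factor-by-treatment interaction rejected in 5% of 1000 simulated studies, its nominal level. The main effect among treated patients alone was significant in 99.6%.

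**The case against.** The authors are open about the root cause. Limitations of study names the missing comparison group and residual confounding and suggests embedding pragmatic randomised trials later. The Discussion presents the registry as a supplement to randomised trials. This stands, and it reduces the point to a mismatch between claims and design. It does not remove it: the remedy offered is matching between regimens, which does nothing for baseline-factor models fitted among treated patients. Neither natural course nor regression to the mean is named, and the third objective is not narrowed.

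Three stronger readings are tempting, and the documents do not support them.

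- *The regimen findings fail for the same reason.* The abstract says "Fundamental factors affecting the clinical effectiveness of acupuncture and the preferred acupuncture regimen in the treatment of CLBP will be identified". The regimen part of that sentence, and the implementation part of the second objective, are served by matched comparisons in which both sides receive acupuncture. Natural course and regression to the mean largely cancel there if matching succeeds.
- *Severe or flare patients will be written into guidelines as suited to acupuncture.* The guideline sentence in the Discussion is about choice of acupoints. Nothing in the article says that severe patients will be labelled in this way.
- *The average fall in pain is inflated by a known amount.* That requires a minimum score at entry, and the article sets none. Without one, the simulated mean fall is zero. An assumed entry at NRS 5 or more would give 34%, 20% and 13% effective for the three rows above, but these are not figures for this protocol. Patients attending selectively during flares would act like a threshold and raise the rate. The article does not quantify how often that happens.

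Interaction terms, and the choice of leading model, are details that a condensed article may leave to the full plan. The wording of objectives and claims is not.

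**Conclusion.** The point holds for the third objective, for the aim of evaluating acupuncture's effectiveness, and for the Discussion's promise to identify cases in which acupuncture does not work. The planned logistic and hierarchical models can identify factors associated with improvement among patients receiving acupuncture, and no more. It bears much less on the matched regimen comparisons.

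The direction follows from the design alone. The size rests on assumptions: zero effect, no trend, mean NRS 5 and correlation 0.49 to 0.85 give 24% to 10% effective on NRS from fluctuation alone, and a severity odds ratio of 3.9 to 2.2 from regression to the mean alone. The artefact weakens as scores become more stable between visits, but it does not vanish within that range.

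**What to change.** 1. Reword the third objective, the effectiveness aim in the abstract and the Discussion's sentence on ineffective cases, so that they speak of prognostic factors for improvement among patients receiving acupuncture.
2. Add to Limitations of study that before-after change and the effective rate include natural course, co-treatment and regression to the mean, and cannot be attributed to acupuncture.
3. Make follow-up NRS and ODI, adjusted for the baseline score, the main predictor model, with the yes/no effective outcome in support. This removes the mechanical link with severity. It does not turn prognostic factors into predictors of benefit from acupuncture.
4. Optionally, add regimen-by-subtype interactions within the matched comparisons, labelled exploratory. There a comparator exists, and the question becomes who does better on which regimen.

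No new data are needed: Table 2 already schedules NRS and ODI at the first visit, the last visit and follow-up. The study is still recruiting, so the text can be changed before analysis. The cost is that the claims become more modest.

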## Methods

### Study setting

The Registry project of Acupuncture was firstly proposed and inspired at 8th World Conference on Acupuncture WFAS SYDNEY 2013 [29]. According to the principles and framework demonstrated by the Agency for Healthcare Research and Quality [30]. China Association of Acupuncture-Moxibustion (CAAM) had established an Acupuncture Patient Registration Alliance and initiated a network database platform-International Registry Platform of Acupuncture-Moxibustion (IRPAM) in 2017. Application of browser/server architecture based on cloud platform mode and Oracle database development to construct the interactive network database platform.

The present protocol partially referenced the guideline of the SPIRIT-PRO Extension Checklist [31] and Registries for Evaluating Patient Outcomes: A User’ guide 3th [30]. The technical roadmap is shown in Fig. 1.

**Fig. 1 Fig1:**
[figure not shown]
Flow chart of study

### Eligibility criteria

#### Requirements for recruiting physicians

Acupuncture practitioners participating in the study should have the following qualifications:
Engaged in acupuncture related clinical practice > for 5 years;Have a certain amount of outpatient volume of patients with CLBP;Prepare individual computer can access to the network;Volunteer to participate and sign a memorandum of understanding.

### Patient source

Patients with CLBP were enrolled continuously to reduce selection bias. All recruited patients will be registered dynamically by the acupuncture physicians. The diagnostic criteria, inclusion criteria and exclusion criteria as follows.

### Diagnostic criteria

Pain or muscle tension in the area below the chest and above the buttocks, with or without pain in the lower extremities, and the pain lasts for more than 12 weeks [32].

### Inclusion criteria

Chronic low back pain or acute onset of chronic low back pain were observed as the main objects to meet the diagnostic criteria for chronic low back pain.16 years≤Age ≤ 80 years;The main treatment method is acupuncture.Voluntarily participate in the patient registration study and sign informed consent.

### Exclusion criteria

Patients with severe systemic diseases, such as primary diseases of cardiovascular, liver, kidney and hematopoietic system, and severe mental disorders;Patients with backache caused by tumor, tuberculosis, cyst and other reasons.

### Outcome measures

#### Primary outcomes

Considering the convenience of real-world measurements, self-reported disability and pain preferable with CLBP. Therefore, Numerical Rating scale (NRS) [33] and Oswestry Disability Index (ODI) [34] were selected as primary outcomes. These two indexes have been confirmed good validity and reliability in the aspects of back-related pain and disability [35, 36].

### Numerical rating scale (NRS)

Patients were asked to use the numbers 0–10 to quantify pain, with ‘0’ symbolize no pain and ‘10’ symbolize most pain. Higher the number, heavier the pain.

### Oswestry disability index (ODI)

The ODI instrument contains 1 item on pain and 9 items on the activities of daily living (daily activities, lift weights, walk, sit, stand, sleep, and social activities, travel and sex). Each entry from 0 to 5 points to calculate, the cumulative score will be added 2 times and the total score range of 0–100 points. Higher the score, lower the back function.

#### Effective rate

Minimal clinically important difference (MCID) is an index to identify effective group, that is the NRS score decreased by 2 points or ODI score cut down 10 points [36]. The effective number divides the total number of people included in the analysis is the effective rate.

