### Participant timeline

As a dynamic registry design, we plan to stick to the registry for at least 2 to 5 years. The tolerance range of time is 3 days around the follow-up point. If the patient does not return after the last visit, follow-up is done by phone within 1 week. At least ensure follow-up at these three time points,1 week, 4 weeks and 12 weeks. Contents of follow-up: whether there is a recurrence, whether there is back pain related surgery, whether there is any other treatment.

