	CLBP Information	Indispensable	Visit date, Chief complaint, Course of disease, Location of pain, Characteristics of pain, causes of pain aggravation, Medical history, Causes of pain relief, Back function, Concomitant symptoms, History of acupuncture and Reception, auxiliary examination
	Diagnosis information	Indispensable	Disease diagnosis, Syndrome differentiation of TCM etiology and meridians, Complicating disease
	Lumbar imaging	Optional	X ray, CT examination, Magnetic Resonance Imaging
	Informed Consent	Indispensable	NA
Acupuncture treatment process	Acupuncture rationale	Indispensable	Acupuncture date, Acupuncture style, Acupoint selection principle, Operation of acupoints
	Acupuncture details	Indispensable	Response elicited, Needle retention time, Needle stimulation, Needle type (gauge, length), Adjunctive therapy, Needle parameter, Co-intervention
	Acupuncture regimen	Indispensable	Number of treatment session, Frequency of treatment
	Combined therapy	Indispensable	Pharmacotherapy, Non-pharmaceutical therapy, Other acupuncture type
Outcomes	Effectiveness evaluation	Indispensable	NRS, ODI, Effective Rate
	Safety evaluation	Indispensable	Adverse events
	Follow up	Indispensable	Disease status (Recurrence, Lower back pain related surgery, Seeking other treatments)

*CT* Computed tomography, *NA* Not applicable, *NRS* Numeric rating scale, *ODI* Oswestry disability index, *TCM* Traditional Chinese Medicine

Considering the characteristics and clinical practice of acupuncture therapies, we referenced Standards for Reporting Interventions in Clinical Trials of Acupuncture (STRICTA) [27] to building data dictionaries and frameworks. Structured, standardized, and logical metadata will be accumulated to reflect the real clinical process of acupuncture treatment for CLBP. Baseline demographic data, CLBP characteristics, patient-centered outcomes of the effectiveness and safety will be truthfully recorded. Specific data element entry and minimum dataset in the register can be found in Table 2. Acupuncture treatment and combined treatment should be recorded at each visit. Changes in symptoms, ODI, and NRS scores were recorded before and after treatment for effectiveness evaluation.

**Table 2 Tab2:** Timetable for data collection

Data elements	Therapeutic Session					Follow-up Period			
	Minimum treatment^a^			…	Last Visit	Minimum follow-up^b^			…
	First Visit	Second Visit	Thirdly Visit			Week 1	Week 12	Week 24	
Demographic information	✓								

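### The post-treatment effective rate credits acupuncture with improvements that follow back surgery or another treatment begun after the last acupuncture visit

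*Protocol article*

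**What the plan says.** The Abstract gives the effective rate primary status: "Numeric rating scale (NRS), Oswestry Disability Index (ODI) and Effective rate will be measured in pain and functional disability assessment, respectively, as the primary outcome". The Effective rate section defines success as "that is the NRS score decreased by 2 points or ODI score cut down 10 points" and fixes the denominator: "The effective number divides the total number of people included in the analysis is the effective rate". Neither sentence sets a condition on what else the patient received.

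On timing, the Abstract says "Evaluation index will be collected at the baseline and follow-up in 1, 4, 12 weeks after the last visit", and the Analytic approach says "We will select 1-week,4-week,12-week, assessments respectively at evaluation time point on the ODI and NRS index". Table 2 also schedules NRS and ODI at the Last Visit.

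On later care, the Participant timeline requires "Contents of follow-up: whether there is a recurrence, whether there is back pain related surgery, whether there is any other treatment". Table 1 lists the same items as indispensable under Outcomes: "Disease status (Recurrence, Lower back pain related surgery, Seeking other treatments".

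On use in the analysis, the Analytic approach plans conditional logistic models to "identify predictors of long-term effectiveness presented by ODI and NRS or recurrence at the12-week follow-up". Of the three follow-up items, only recurrence is named there, and it is named as an outcome. Surgery and other treatment are given no analytic role anywhere.

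**The concern.** After the last acupuncture visit patients are free to seek other care, and those who gained least from acupuncture have most reason to do so. Take a patient in whom acupuncture failed, who then had surgery or began another treatment, and whose NRS is 2 points lower at week 12. Under the rule as written, that patient is an acupuncture success in the effective rate and an effective case in the week-12 predictor model.

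This runs against the registry's own aims. The objectives at the end of the Background are to find what drives the effectiveness of acupuncture and which patients it suits. The Discussion adds the aim of characterising cases in which acupuncture did not work. A failure rescued by other care is such a case, yet it enters on the success side. The Limitations section concedes that there is no predefined comparison group, so nothing offsets the effect on the overall rate. In the predictor models, characteristics linked to access to surgery or other treatment could appear as predictors of response to acupuncture.

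**Working it through.** The plan has no figure of its own to reproduce here: it gives no expected effective rate and no expected frequency of surgery or other treatment. The check has two parts.

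**1. Does any rule in the document change the classification?**
- Effective rate section: score change only.
- Exclusions in the Analytic approach: poor compliance, departure from the study programme, or missing important information. Later care is not named, and it is an expected, recorded item in an observational study, so it is not clearly a departure.
- Matching and regression: baseline variables and the propensity score.
- Week-12 models: recurrence is named as an outcome; surgery and other treatment are not mentioned.

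Nothing alters the result of the score-only rule.

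**2. How far apart are the two ways of counting?** All three inputs are assumptions:
- u = share of analysed patients with surgery or a new treatment between the last visit and the assessment
- r = share of those who meet the NRS or ODI threshold
- p = effective rate in the remaining patients, set at 50%

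Score-only rate = (1 − u)p + ur. Rate with these patients counted as not effective = (1 − u)p. The gap is u × r, whatever the value of p.

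| u | r | Score-only | Counted as not effective | Gap (points) | Patients of 2000 |
|---|---|---|---|---|---|
| 5% | 30% | 49.0% | 47.5% | 1.5 | 30 |
| 10% | 50% | 50.0% | 45.0% | 5 | 100 |
| 20% | 50% | 50.0% | 40.0% | 10 | 200 |
| 30% | 70% | 56.0% | 35.0% | 21 | 420 |

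For the last row: 0.70 × 0.50 + 0.30 × 0.70 = 0.56, against 0.70 × 0.50 = 0.35. The last column is 2000 × u × r, using the planned minimum sample.

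The gap is the excess over the stricter count. It is not a measured bias: some of these patients would have met the threshold without the later care, so the wrongly credited part is at most u × r.

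Dropping these patients would not solve the problem. The rate would become (1 − u)p / (1 − u) = p. With u = 20% and r = 50% that is 50%, the same as score-only, because the failures leave the denominator.

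**The case against.** **This is a condensed article, and handling of post-treatment events belongs in an analysis plan.** That would answer a complaint about a missing detail. Here the classification rule is stated, with numerator and denominator, and applying it as written gives the result described. It remains true that the article nowhere says in words that such patients are scored effective; this follows from the definition and the absence of any other rule.

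**Counting outcomes regardless of later care is legitimate in a real-world registry.** It is, and this stands in part. But the plan does not declare that choice, and the result would then describe acupuncture plus later care, while the text speaks of the effectiveness of acupuncture.

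**The week-12 models adjust for unlisted variables, which might include later treatment.** This cannot be ruled out. Adjustment would still leave the outcome itself scored as a success, and it would condition on an event that treatment failure may have caused.

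**Counting all later care as failure also misclassifies.** This stands. Suppose true rates of 60% and 45%, with 20% of true responders adding another treatment (assumed). The stricter rule records 0.60 × 0.8 = 48% and 0.45 × 0.8 = 36%. Both are too low, and the difference falls from 15 to 12 points. The stricter rule should therefore not stand alone.

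Three stronger readings are tempting, and the document does not support them:
- *All effectiveness readings are affected.* Table 2 includes NRS and ODI at the Last Visit, before any post-treatment care.
- *Every patient with later surgery or treatment is scored effective.* The patient must still meet the threshold.
- *The propensity-matched comparisons of responder rates shrink.* If 40% of non-responders sought other care and half of those crossed the threshold, 60% against 45% would be recorded as 0.60 + 0.40 × 0.4 × 0.5 = 68% against 0.45 + 0.55 × 0.4 × 0.5 = 56%. But the Analytic approach compares matched groups on change in ODI and NRS by paired t-test, so this arithmetic does not describe that analysis.

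**Conclusion.** The point holds for the effective rate after the end of treatment and for the week-12 predictor models. As written, both can count improvement that follows surgery or a newly started treatment as a success of acupuncture, although the data needed to separate such patients are largely collected already. The direction for the overall rate is upward. Weeks 4 and 12 are the most exposed; week 1 is exposed too, over a shorter interval.

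The size is not known. The range of 1.5 to 21 points rests entirely on assumed uptake (5–30%) and assumed threshold-crossing (30–70%), and it measures the gap between two ways of counting. It shows that the choice can matter for a primary outcome, not that it will. It supports a change to the plan before analysis. It does not support declaring the score-only rate invalid.

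**What to change.** In the Effective rate section and in the description of the week-12 predictor models, prespecify two versions of the post-treatment result:

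1. Patients with back-pain surgery, or a new back-pain treatment started after the last acupuncture visit and before the assessment, count as not effective at that and later time points.
2. Score-only, as now, labelled as the effect of acupuncture plus later care.

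Report the two side by side. Add a start date to the existing follow-up question on surgery and other treatment. Without it, later care cannot be placed before or after an assessment, since Table 2 stops recording combined therapy at the last visit. The follow-up weeks also need reconciling, because Table 2 shows weeks 1, 12 and 24 while the Abstract, Participant timeline and Analytic approach give 1, 4 and 12.

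The cost is a few sentences and one date field. The downside is a somewhat lower stated rate in the first version, which can also class true responders who add another treatment as failures. That is why both versions are needed.
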